## Study design and methodology

### Screening and study participants

From January 2024 to January 2026 all women presenting with risk for preterm birth (e.g. cervical shortening, PPROM, vaginal bleeding, preeclampsia, HELLP syndrome) are informed about the study and asked to participate after giving their written informed consent. The women will be given probiotics from the day that they are identified with a risk of imminent preterm birth and decide to participate in this study until the delivery of the infant. We will include approximately 130 women from 20 + 0 to 36 + 6 weeks of pregnancy. The study population will be randomly divided into two groups consisting of (1) women taking probiotics during pregnancy and (2) women without probiotic supplementation. This study is registered at the German Registry for clinical studies (DRKS), DRKS00033539.

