### Intervention/Control

Study participants are randomly assigned to receive the probiotic mixture (intervention group *n* = 73) or not (control group *n* = 73). The intervention is one capsule of Bactiol^®^ Infantis per day until delivery. The proposed number of participants is calculated based on former studies (see below). A randomization sequence was created in advance to assign mother – infant pairs to a study arm. This trial is not blinded. The women and participating doctors know whether they are in the intervention or control group, and we are not using a placebo.

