### Estimated sample size and power calculations

Based on the publication of Seppo et al. [1] who supplemented probiotics in pregnancies > 36th weeks calculations of sample sizes were performed.

**Table 2 Tab2:** Calculation minimal sample size based on data from Seppo et al. 2019 [1]

Human milk oligosaccharids	Supplementation	No supplementation	Minimal sample size
	mean [SD]	mean [SD]	*n*
3-fucosyllactose (µmol/mL)	413 [164]	312 [232]	73
3´-sialyllactose (µmol/mL)	833 [679]	516 [378]	55
difucosyllacto-*N*-hexaose (µmol/mL)	62.0 [43.3]	93.7 [47.7]	38
lacto-*N*-tetraose (µmol/mL)	509 [339]	861 [563]	32
lacto-*N*-fucopentaose I (µmol/mL)	2000 [585]	2450 [836]	47
6´-sialyllactose (µmol/mL)	472 [159]	567 [179]	58

*Legend SD* standard deviation; *n* estimated sample size

Table 2. lists HMO measurement means and standard deviations taken from Seppo et al. [1] for six different HMO subgroups. Column titled “n” lists minimal sample size numbers inferred via balanced Mann-Whitney U test. Calculations were performed with the R package ’pwrss’ [Bulus, M. (2023). pwrss: Statistical Power and Sample Size Calculation Tools. R package version 0.3.1.]. The significance threshold (acceptable type I error rate) was set to alpha = 0.05 and predictive power (acceptable Type II error rate) was set to 0.8. Dropout rate was considered to be 10%. Whereas sample size numbers in Seppo et al. [1] are unbalanced between treatment group and control group (50 vs. 31), we assumed balanced conditions in our analysis to minimize the total number of required samples. Based on these calculations we include 73 women taking the probiotics ( ≙ verum group) during pregnancy and 73 women without treatment ( ≙ control group). We choose the maximal calculated number n (Table 2.) as minimal sample size and add a 25% risk of drop out.

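### The number of women to be included is given as about 130 in one section and as 73 + 73 = 146 in two others, with no reconciliation; for 3-fucosyllactose, including only 130 would mean about 75% power at 10% drop-out instead of about 80%

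*Protocol article*

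**What the plan says.** The inclusion total appears in three sections of the protocol article.

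- **Screening and study participants:** "We will include approximately 130 women from 20 + 0 to 36 + 6 weeks of pregnancy". The sentence that follows splits this population at random into two groups, so 130 reads as the number randomised, or 65 per arm.
- **Intervention/Control:** "intervention group *n* = 73) or not (control group *n* = 73", which makes 146.
- **Estimated sample size and power calculations:** "Based on these calculations we include 73 women taking the probiotics", with the same number of untreated controls, again 146.

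The sample size section also gives the design inputs. On the error rate: "The significance threshold (acceptable type I error rate) was set to alpha = 0.05". On power: "predictive power (acceptable Type II error rate) was set to 0.8". Table 2 "lists minimal sample size numbers inferred via balanced Mann-Whitney U test". Drop-out is given twice: first as 10% ("Dropout rate was considered to be 10", in per cent), and at the end of the section as a 25% risk to be added to the largest number in the table.

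**The concern.** The same verb, include, is attached to two totals that differ by 16 women, which is 11% of 146. Calling 130 approximate does not close that gap, and no section labels it as evaluable, completed or interim. A reader of the final report could not tell whether a trial that ended at 130 had met its target or missed it.

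The gap also matters for power. If 73 per arm already contains the drop-out allowance, a trial that includes 65 per arm has none left, and any loss takes the limiting endpoint below the stated 80%.

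**Working it through.** **Inputs (Table 2 and the text below it).** 3-fucosyllactose: 413 [164] with supplementation, 312 [232] without. 3'-sialyllactose: 833 [679] and 516 [378]. Alpha 0.05, power 0.80, Mann-Whitney test, equal arms, drop-out 10% or 25%. Sidedness is not stated.

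**Step 1: reproduce the stated 73.** Take the SD as the root mean square of the two group SDs and use

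n per arm = 2 × (SD × (1.960 + 0.842) / difference)² ÷ (3/π) ÷ (1 − drop-out).

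For 3-fucosyllactose:
- SD = √((164² + 232²)/2) = 200.9; difference = 101; standardised difference 101/200.9 = 0.503.
- Normal-theory n = 62.1 per arm.
- Divided by the Mann-Whitney efficiency 3/π: 65.0 per arm.
- Divided by 0.9: 72.3, rounded up to 73, as stated.

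The same steps give 55, 38, 32 and 47 for the next four rows of Table 2, and 58.0 for the last row, stated as 58. Two alternatives fail. A one-sided test gives 51.2 / 0.9 = 56.9, so 57. A 25% loss on 65.0 gives 65.04 / 0.75 = 86.7, so 87. Hence 73 comes from a two-sided test and already holds the 10% allowance. Before that allowance the requirement is 2 × 65.0 = 130.

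**Step 2: power for each total.** Power is taken from the noncentral t distribution with n × 3/π women per arm, two-sided 0.05, with standardised differences of 0.503 (3-fucosyllactose) and 317/549.5 = 0.577 (3'-sialyllactose).

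| Included | Drop-out | Evaluable per arm | 3-fucosyllactose | 3'-sialyllactose |
|---|---|---|---|---|
| 130 | none | 65 | 79.4% | 89.0% |
| 130 | 10% | 65 × 0.90 = 58.5 | 75.0% | 85.6% |
| 130 | 25% | 65 × 0.75 = 48.75 | 67.0% | 78.6% |
| 146 | 10% | 73 × 0.90 = 65.7 | 79.8% | 89.4% |
| 146 | 25% | 73 × 0.75 = 54.75 | 72.1% | 83.2% |

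**Step 3: check.** For 3-fucosyllactose with 130 included, the normal approximation and the Noether formula give 74% to 76% at 10% drop-out and 66% to 68% at 25%. A simulation of the Mann-Whitney test (20,000 runs, normal data with the stated SDs) gives 73.9% and 75.7% at 58 and 59 per arm, and 66.3% and 66.8% at 48 and 49.

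**Step 4: separate the two causes.** For 3-fucosyllactose, moving from 146 to 130 costs 79.8 − 75.0 = 4.8 points at 10% drop-out and 72.1 − 67.0 = 5.1 points at 25%. Moving from 10% to 25% drop-out costs 79.8 − 72.1 = 7.7 points at 146 and 75.0 − 67.0 = 8.0 points at 130.

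**The case against.** The best defence is that the formal target can be identified. The allocation section and the sample size section agree on 73 per arm, and only the screening paragraph, with a hedged figure, says 130. Since 2 × 65.0 is 130, that figure may simply be the evaluable number from the same calculation under a loose verb. If so, the slip is one of labelling and the power is untouched. This is plausible, but it remains an inference: the screening section says these women are included and then randomised. The contradiction on the page stands.

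Four stronger readings are tempting, and the article does not support them.

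- *Recruitment will stop at 130, so the trial is underpowered.* The article gives a recruitment window, January 2024 to January 2026, and no rule that closes recruitment at a count. The 75% and 67% are conditional on only 130 being included.
- *Power fails for the primary endpoint as a whole.* The shortfall is for 3-fucosyllactose. With 130 women 3'-sialyllactose keeps 85.6% at 10% drop-out and falls just under 80% (78.6%) only at 25%.
- *The discrepancy explains the fall to 67%.* It accounts for about 5 points. About 8 more come from the separate conflict between 10% and 25% drop-out.
- *Writing 146 everywhere secures 80%.* It does so only if drop-out is 10%. At 25%, 146 women give about 72% for 3-fucosyllactose.

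**Conclusion.** The article is wrong as written: a sample size on which the trial relies is stated as about 130 and as 146, and nothing reconciles the two. If only 130 were included, power for 3-fucosyllactose would be about 75% at 10% drop-out and 67% at 25%, against about 80% and 72% with 146. If 146 is the target in use, the harm is confined to the text; the article alone does not show which total is in use.

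The figures rest on the Table 2 means and SDs, equal arms, and a two-sided test. The last is inferred from the reproduction of Table 2. A one-sided test would give about 84% and 78% for 130 women, but it does not yield the stated 73.

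**What to change.** State one inclusion total in all three sections, and settle the 10% or 25% drop-out rate in the sample size section in the same edit, because the total has no fixed meaning without it.

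- **If 10% holds:** in Screening and study participants, replace 130 by 146 randomised (73 per arm), about 130 evaluable (146 × 0.9 = 131.4), and remove the 25% statement.
- **If 130 is the real recruitment limit:** give 130 (65 per arm) in all three sections and restate power for 3-fucosyllactose as about 75% at 10% drop-out or 67% at 25%.
- **If 146 is kept but 25% drop-out is expected:** restate power for 3-fucosyllactose as about 72%.

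If 146 is already the working target and 10% the working drop-out rate, the cost is a few words. In the other cases it is a lower stated power, with no change to the design.

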### In- and exclusion criteria

Pregnant women of any ethnic background between 20 + 0 and 36 + 6 weeks of pregnancy who are at risk for preterm birth are included. The underlying condition (e.g. PPROM, cervical shortening, bleeding, preeclampsia, HELLP syndrome) is not decisive to inclusion. Participating patients will be included after they have been informed about the study procedures, intervention, associated responsibilities and when they have given written informed consent. Women with outpatient monitoring are also applicable for participation. Since the date of birth cannot be predicted, the study concept inevitably includes full-term children – mother pairs to be included. Pregnant women under the age of 18 years and women, who do not plan to deliver their infant at our site will be excluded primarily, because in these cases collecting the samples postpartum is not feasible. Women who decline to feed their infant with breast milk or without written consent will also be excluded.

### Probiotic formula

The probiotic formulation is Bactiol^®^ Infantis consisting of *Bifidobacterium longum* subsp. *Infantis*,* B. animalis* subsp. *Lactis (BB-12) and Lactobacillus acidophilus (La-5)*. These strains have been commonly used in former studies supplementing preterm infants [51–53]. The women are provided a single dose capsule once daily. Each dose contains 4.5 × 10^9^ colony forming units of the bacteria mixture. We chose this particular formula because it has been previously used in clinical trials. The multistrain probiotics raised no safety concerns in large observational studies in preterm infants and the PRIMAL trial [52] and is approved for use in pregnancy. Several strains of lactobacilli are also able to utilize HMOs, but with less capacity compared to Bifidobacteria [60]. Lactobacillus acidophilus has the ability to hydrolyze HMOs and studies report moderate growth of Lactobacillus acidophilus (LA-5) on lacto-N-neotetraose and on lactose [61, 62].

### Intervention/Control

Study participants are randomly assigned to receive the probiotic mixture (intervention group *n* = 73) or not (control group *n* = 73). The intervention is one capsule of Bactiol^®^ Infantis per day until delivery. The proposed number of participants is calculated based on former studies (see below). A randomization sequence was created in advance to assign mother – infant pairs to a study arm. This trial is not blinded. The women and participating doctors know whether they are in the intervention or control group, and we are not using a placebo.

### Stopping rules

Any participating women may be retired from the study at any time at her own request, unbiased by reason and without facing any disadvantages of clinical support. Women who are withdrawn from the study, are not allowed to re-enter the study. The responsible doctor has the right to exclude women from the study, who deliver at another hospital and women with discontinuous intake of the probiotics in more than 30% of days until delivery. To ensure that the data is recorded according to the intention-to-treat principle, all patients should be followed up and documented after retirement from the study.

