### Primary endpoint, secondary endpoints/data collection

The primary endpoint is the HMO composition (3-fucosyllactose, 3’-sialyllactose) in human breast milk after supplementation prenatally. Secondary endpoints are clinical and safety outcomes of mothers (infections, alterations in vaginal microbiome) and infants (preterm birth, sepsis, growth, gastrointestinal complications) and the effects on the microbiome composition in the rectovaginal tract of mothers at delivery and in the gut of term and preterm infants.

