### Data collection

Standardized Case Report Forms (CRFs) are used to record information from the mother prenatally and postnatally from mother and infant. At the time of inclusion (CRF inclusion), closely after birth (CRF day 3), one month after birth (CRF day 28), at three months CRF 3 m (mother + infant), one- and five-year follow- up (CRF 12 and 60 m) (see Fig. 2).

Data collected at the follow-ups will be used to measure long-term outcomes (allergies, incidence of infections, re-admissions to the hospital). The CRFs are filled in manually by the study team (neonatologist, doctoral student and study nurse). Additionally, the women will be asked to keep a diary handed out at inclusion to document regularity of probiotic intake, infections, antibiotic therapy, allergies and possible side effects during the intake of probiotics. The inclusion-CRF collects information of former participant’s medical history e.g. preexistent diseases, the course of pregnancy, former pregnancies and allergies. The follow up CRFs collect data from both, mothers and infants. CRF day 3 includes information about the delivery mode, reason for delivery, infections and risk factors for microbiome dysbiosis. In CRF day 28 information about complications in puerperium, growth parameters and feeding of the infant is collected. This data will be collected via telephone interview. In case of birth before completed 32 weeks follow-up examination will take place onsite. At follow-up information on both, mother and infant will be recorded via CRFs.

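### A doctor who knows the arm may exclude randomised women for delivering at another hospital, which conflicts with the intention-to-treat sentence that follows and leaves their place in the analysis open

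*Protocol article*

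**What the plan says.** Four parts of the protocol article bear on this.

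- **In- and exclusion criteria.** Delivery site is an entry criterion: "women, who do not plan to deliver their infant at our site will be excluded primarily". The reason given is that postpartum samples could not then be collected. The same section adds: "Women with outpatient monitoring are also applicable for participation".
- **Stopping rules.** A second rule acts after randomisation, on where the birth took place: "The responsible doctor has the right to exclude women from the study, who deliver at another hospital". The same sentence gives a second ground, "women with discontinuous intake of the probiotics in more than 30% of days until delivery", which can remove only women in the probiotic arm and is a separate matter. The section then says that, to keep to intention to treat, "all patients should be followed up and documented after retirement from the study".
- **Intervention/Control.** The trial is open: "The women and participating doctors know whether they are in the intervention or control group".
- **Primary endpoint, secondary endpoints/data collection.** The primary endpoint is milk oligosaccharide composition. Secondary endpoints include outcomes of "infants (preterm birth, sepsis, growth, gastrointestinal complications".

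On data routes, the Data collection section says of the day-28 form: "This data will be collected via telephone interview". It adds that after birth before 32 completed weeks the follow-up examination is onsite.

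**The concern.** Screening on the plan to deliver at the site is sound, because the plan is known before randomisation. Excluding on the actual place of birth is different. It is an event after randomisation, plausibly tied to the timing and course of labour. A fast preterm labour may end at the nearest hospital. A woman monitored as an outpatient whose risk settles may deliver locally at term. The article gives no data on either pattern, but both are foreseeable in this population.

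No criterion says when the right is used, and the person using it knows the arm. The sampling difficulty that justifies the entry criterion does not justify dropping gestational age at birth, sepsis, growth or gastrointestinal complications, none of which needs a sample taken on site.

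At stake is whether these secondary outcomes are compared in all randomised women or only in those left after a selection related to the outcomes.

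**Working it through.** **1. Reading the two sentences together.** One sentence lets the doctor exclude a woman from the study. The next wants all patients followed after retirement, for intention to treat. Two readings are possible:

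- *Reading A:* exclusion ends participation, data collection continues, and the woman is analysed in her arm. The right to exclude then does nothing for the clinical outcomes and need not exist.
- *Reading B:* the woman leaves the study and the analysis. The intention-to-treat sentence is then not met.

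The section does not settle which applies. It uses its word for retirement for withdrawal at the woman's own request and a different word for the doctor's act. The follow-up sentence concerns recording and is silent on analysis.

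**2. Size under reading B.** The plan has no figure to reproduce here: it gives no rate of preterm birth, of delivery elsewhere or of exclusion. All rates below are assumptions, with no true effect on preterm birth.

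Let p be the true preterm rate, e_p the probability of exclusion after preterm birth and e_t after term birth. Among women who remain:

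observed rate = p(1 − e_p) / [p(1 − e_p) + (1 − p)(1 − e_t)]

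With p = 0.5:

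| Exclusion, first arm (e_p / e_t) | Exclusion, second arm (e_p / e_t) | Observed rates | Difference |
|---|---|---|---|
| 10% / 10% | 10% / 10% | 0.45/0.90 = 0.500 in both | 0 |
| 2% / 18% | 2% / 18% | 0.49/0.90 = 0.544 in both | 0 |
| 2% / 18% | 10% / 10% | 0.544 v 0.500 | 0.044 |
| 0% / 20% | 20% / 0% | 0.50/0.90 = 0.556 v 0.40/0.90 = 0.444 | 0.111 |

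Varying p:

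- Selection in one arm (third row): 0.339 − 0.300 = 0.039 at p = 0.3, and 0.736 − 0.700 = 0.036 at p = 0.7.
- Extreme opposing selection (fourth row): 0.349 − 0.255 = 0.094 at p = 0.3, and 0.745 − 0.651 = 0.094 at p = 0.7.

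**3. The same in whole women.** Take the planned 73 per arm (Intervention/Control), and assume 37 preterm births in each (37/73 = 50.7%) and 11 excluded per arm.

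- If both arms lose 3 preterm and 8 term births, both show (37 − 3)/(73 − 11) = 34/62 = 54.8%. The absolute rate moves by about 4 points and the contrast stays at zero.
- If the second arm instead loses 8 preterm and 3 term births, it shows (37 − 8)/62 = 29/62 = 46.8%. The false difference is then about 8 points.

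**4. Size under reading A.** With everyone followed and analysed as randomised, nothing is removed and the distortion of the preterm-birth comparison is zero.

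**The case against.** The strongest reply is that the safeguard is already on the page: the sentence after the exclusion right asks for follow-up of all patients. A reader might infer that the rule as written biases the preterm-birth and infant comparisons and that no analysis could repair this. The article does not support that inference. If the follow-up is done and the women are analysed, the bias in preterm birth does not arise.

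Three further points against the stronger reading stand:

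- The rule covers both arms. Dependence on birth timing alone gives no false difference under the null. The larger figures above come from opposing losses that are assumed, not shown. The entry criterion should also keep deliveries elsewhere uncommon.
- It would go too far to say that the day-28 contact never depends on place of birth, because births before 32 weeks are followed up onsite.
- The primary endpoint gains little. Early milk would largely be missing for these women under either rule.

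One reply stands only in part. Analysis sets can properly be left to the statistical analysis plan. But a right to exclude from the study governs which data are collected, and an analysis plan cannot restore outcomes that nobody recorded. The clash with the intention-to-treat sentence is in the protocol text itself. A dropout allowance in the sample size covers numbers lost, not selective loss.

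**Conclusion.** The point holds as a conflict in the text with a conditional risk. A discretionary, unblinded exclusion on an event after randomisation stands next to an intention-to-treat statement it does not fit, and the article does not say that excluded women remain in the analysis.

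If they are left out, two things can follow. Absolute preterm rates shift, by about 4 points under the assumed 2% and 18% exclusion. A false difference between arms appears if exclusion differs by arm: about 4 points for selection in one arm, and 9 to 11 points in the extreme opposing case. Unblinded discretion is one way for exclusion to come to differ by arm; an effect of the intervention on birth timing is another. Actual size and direction are unknown, because the article gives no rates.

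The risk concerns preterm birth and the clinical infant outcomes, all secondary. It does not show that the trial's comparisons are biased.

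**What to change.** - Remove delivery at another hospital as a reason for exclusion after randomisation. Keep planned delivery site as an entry criterion only.
- State that women who deliver elsewhere stay in their randomised arm for follow-up and analysis.
- Collect gestational age at birth and the clinical infant outcomes through the follow-up that Stopping rules already foresees: the existing case report forms and telephone contact, with outside hospital records where needed, including for births before 32 weeks.
- Treat milk, swab and stool samples that could not be collected as missing data, not as grounds for exclusion.
- Report the number of such women by arm.

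The cost is about one sentence in the protocol and a few record requests. Early samples will still be missing for these women. The change is best made before the right is used, because outcomes that were not recorded may be hard to recover later.

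### A discretionary exclusion for missed capsules can act only on the probiotic arm, and the protocol does not say that excluded women stay in the primary analysis as randomised

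*Protocol article*

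**What the plan says.** All places are in the protocol article.

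- *Stopping rules*: "The responsible doctor has the right to exclude women from the study". Two groups are named: women who deliver at another hospital, and "women with discontinuous intake of the probiotics in more than 30% of days until delivery". A withdrawn woman may not re-enter.
- *Stopping rules*, next sentence: "To ensure that the data is recorded according to the intention-to-treat principle, all patients should be followed up and documented after retirement from the study".
- *Intervention/Control*: "This trial is not blinded", and "The women and participating doctors know whether they are in the intervention or control group, and we are not using a placebo". Allocation is 73 to 73.
- *Screening and study participants*: the comparison group is "women without probiotic supplementation".
- *Sample collection*: milk, which carries the primary endpoint, is collected on days 1, 2, 3, 7, 14 and 28 after birth.
- *Statistical analysis*: analysis details are left to a statistical analysis plan, to be finalised before the last patient is included.

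**The concern.** The intake limb of the rule has four features that do not go well together in a randomised comparison. It uses behaviour after randomisation. It can reach one arm only, because a control woman has no capsules to miss. It is optional rather than automatic. It is applied by someone who knows the allocation and the course of the pregnancy.

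The intention-to-treat sentence does not fully answer this. It secures follow-up and documentation. The primary endpoint, however, is measured in milk samples, and nothing says that sampling continues once a woman has been excluded. Nor does it say that she is counted in her randomised arm.

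At stake is the interpretation of the primary result. If low-intake women drop out of the probiotic arm while their counterparts among the controls stay in, a difference in 3-fucosyllactose or 3'-sialyllactose may partly reflect who was kept and not what the probiotic did.

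**Working it through.** **1. The planned size, as a yardstick.** Table 2 gives 3-fucosyllactose 413 [SD 164] with and 312 [SD 232] without supplementation.

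- SD = sqrt((164² + 232²)/2) = 200.9
- Difference = 101, so d = 101/200.9 = 0.503
- Two-sided alpha 0.05 and power 0.80: n = 2 × ((1.960 + 0.842)/0.503)² = 62.1 per arm
- Mann-Whitney factor π/3: 65.04
- 10% dropout: 65.04/0.90 = 72.27, rounded up to 73

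The stated 73 per arm reproduces. The point does not depend on it. It supplies the planned effect (0.50 SD) and the evaluable number (73 × 0.9 = 65.7, about 66 per arm).

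**2. What the two sentences settle.**

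| Question | Exclusion sentence | Intention-to-treat sentence |
|---|---|---|
| Which arm can it reach? | Intake limb: probiotic only | Both |
| Is it automatic? | No, a right of the doctor | Worded as what should happen |
| Does follow-up continue? | Not stated | Yes, with documentation |
| Does milk sampling continue? | Not stated | Not stated |
| Is she in the primary analysis as randomised? | Not stated | Not stated |

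The last two rows decide whether the comparison is protected, and both are open.

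**3. Size of the bias if excluded women are left out.** Assumptions, none of them given in the documents: a share f of the probiotic arm is excluded; excluded and retained women differ by g SD in the outcome; there is no true effect; about 66 per arm are evaluable before exclusion; every excluded woman is dropped from the analysis.

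- Shift in the contrast = f × g
- SE = sqrt(1/(66(1 − f)) + 1/66)
- Type I error = P(|Z + shift/SE| > 1.96)

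| f | g (SD) | Shift (SD) | SE | Shift/SE | Type I error | Shift as share of 0.503 |
|---|---|---|---|---|---|---|
| 0.10 | 0.3 | 0.03 | 0.179 | 0.17 | 5.3% | 6% |
| 0.20 | 0.5 | 0.10 | 0.185 | 0.54 | 8.4% | 20% |
| 0.30 | 0.8 | 0.24 | 0.192 | 1.25 | 24% | 48% |
| any | 0 | 0 | – | 0 | 5% | 0% |

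**4. Cross-check with a different model.** Drop the lowest-adhering share f of a 73-woman probiotic arm, with adherence correlated ρ with the outcome (f and ρ both assumed), and simulate the test under no effect.

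- f = 10%, ρ = 0.2: shift 0.04 SD, type I error about 5.5%
- f = 20%, ρ = 0.3: shift 0.11 SD, about 9%
- f = 30%, ρ = 0.5: shift 0.25 SD, about 27%
- ρ = 0: no shift, about 5%

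The two models agree in range and in the null case.

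**The case against.** The strongest reply is that nothing here contradicts intention-to-treat. The rule stands under *Stopping rules* and concerns participation. The next sentence keeps every woman under follow-up and says why. Ending participation while still recording outcomes is compatible with analysing everyone as randomised, and analysis populations are normally defined in a statistical analysis plan, which is not shown. Intake is also counted only up to delivery, before any milk is sampled, so adherence status cannot depend on a measured HMO value.

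Much of this stands. A reader might infer that the rule itself breaks the randomised comparison and contradicts intention-to-treat. The text does not support that, since it nowhere says that excluded women leave the primary analysis. The absence of an analysis-set definition is not the point either. What remains is a rule of conduct that the protocol does state. It can be applied before an analysis plan exists, because that plan need only be final before the last inclusion. If exclusion ends milk sampling, no later definition can restore the missing endpoint. And although selection on measured HMO values is ruled out, selection on prognosis is not.

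A reader might also infer that the rule removes mainly early-delivering women, whose milk differs because HMO levels depend on length of gestation. Part of the arithmetic is right: with three or fewer intake days, one missed day is at least 33% and exceeds the threshold. But the denominator is days from enrolment, not gestational age. A woman enrolled at 36+4 who delivers three days later is at 37+0, while one enrolled at 20+0 who delivers at 30+0 has had 70 days. The documents give neither the distribution of intake durations nor the pattern of missed doses, so that inference does not follow.

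Finally, the error rates are conditional. The 24% needs both upper extremes at once, with a gap of 0.8 SD that is larger than the planned effect. The lower end, 5.3%, is practically nominal.

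**Conclusion.** The concern holds in a limited form. The protocol gives unblinded doctors a discretionary, post-randomisation right of exclusion whose intake limb can reach only the probiotic arm. It sets this beside an intention-to-treat statement that secures documentation but neither continued milk sampling nor analysis as randomised. This permits a break of the randomised comparison; it does not by itself cause one.

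Bias needs two conditions: excluded women are left out of the primary analysis, and adherence is related to HMO levels. The documents settle neither. If both hold, assumed exclusion of 10-30% and an assumed gap of 0.3-0.8 SD give a shift of 0.03-0.24 SD (6-48% of the planned 0.50 SD) and a type I error of about 5-24%. If either fails, this mechanism produces no bias. The one-arm character of the rule is certain; the size of its effect is not.

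**What to change.** Reconcile the two sentences in *Stopping rules*. Suggested wording: *Women whose intake falls below the threshold remain in follow-up, give milk samples as scheduled, and are included in the primary analysis in the arm to which they were randomised. The 30% criterion is used only to define a secondary per-protocol set.* This concerns retention and analysis only and leaves the capsule regimen untouched.

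The other limb, delivery at another hospital, can occur in both arms and is a separate matter. It is better handled as missing data in both arms than as exclusion.

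**Cost.** A change of wording, plus milk sampling for women who would otherwise have left; documentation after retirement is already required. The intention-to-treat estimate may be smaller than one restricted to adherent women. As a worst case, assume that a share f of the probiotic arm gets no benefit at all and that 65.7 per arm are evaluable, with the Mann-Whitney allowance (65.7 × 3/π = 62.7). Power is then Φ(0.503(1 − f) × sqrt(62.7/2) − 1.96). It falls from 80% to about 72%, 62% and 50% at f = 10%, 20% and 30%. If partial intake has some effect, the loss is smaller. The per-protocol set still allows the adherent-only estimate to be reported beside the primary one.
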